**VERSION NUMBER/DATE:**

1.0; 01.10.2023

1.1; 12.20.2024      Update to actual study dates. Correct statistical plan consistent with actual number of statistical tests (See also <https://osf.io/9g58j>).

## 2. STUDY OBJECTIVES

The proposed parallel-group randomized clinical trial will test the efficacy of the Integrated Toolbox for Healthcare Providers (ISTH) on the psychological functioning, well-being, occupational performance, and peripheral inflammation of Mexican healthcare providers.

## 3. BACKGROUND

The COVID-19 pandemic has placed an extraordinary strain on health care systems and providers. According to Amnesty International (Amnesty International, 2021), as of figures compiled by March 5th, 2021, at least 3,371 Mexican healthcare providers (HCPs) have died from COVID-19. These numbers rank Mexico second in the world in terms of total HCP deaths, second only to the United States with 3,507 reported deaths, but with 2.5 times the deaths per capita (2.6 to 1.07 HCP deaths per 100,000 population, respectively). According to the John Hopkins coronavirus resource center, Mexico also has the highest case-fatality ratio in the world with 9 deaths per 100 confirmed cases as of March 27th (John Hopkins Coronavirus Resource Center, 2021). Though these numbers should be interpreted with caution, they point to the alarming effects that the COVID-19 pandemic is having on Mexican HCPs and its healthcare system.

Strategies to mitigate the impacts of COVID-19 on HCP mental health in Mexico have been limited. The COVID-19 pandemic has catalyzed a mental health crisis in the Mexican healthcare system. Hoping to mitigate this issue, Mexican health authorities established call centers offering psychological support for HCPs. Unfortunately, the strategy has had limited impact as evidenced by the low number of calls received in the first six months of the program (less than 200 in the state of Jalisco which has over 25,000 health care workers). Research suggests that HCPs are particularly likely to be deterred from seeking help for mental health problems due to concerns of disclosure/confidentiality, negative social judgement, and stigma (Clement et al., 2015). This resistance to seeking help might be amplified by a culture of ‘invincibility’ within medicine (Henderson et al., 2012). Thus, a less stigmatizing form of care, one that doesn’t talk about mental illness but rather about character strengths, well-being, and how to better cope with stress and burnout, might be a more suitable form of intervention to help HCPs.

### **The Stress Toolbox for Healthcare Providers (STH).**

To address HCP mental health and rooted in the belief that character development is vital to coping with stressful events, to resilience (Harzer & Ruch, 2015), to professional fulfillment (Brown & Gunderman, 2006; Hausler et al., 2017; Kachel, Huber, Strecker, Höge, & Höfer, 2020), and to human flourishing (Peterson & Seligman, 2004; Seligman, 2018), AtentaMente developed the “Stress Toolbox for Health Providers” (STH). The STH is a Zoom-based, 16-hour course (eight x 2-hour weekly sessions) aimed at strengthening four pillars of character that underlie well-being: Awareness, Connection, Insight, and Purpose (ACIP) competencies. Recent evidence suggests that these are key pillars of well-being and critically, that they demonstrate plasticity and therefore the opportunity for intentional training and development (Dahl, Wilson-Mendenhall, & Davidson, 2020). Awareness competencies include attention regulation, mindfulness, and meta-awareness; Connection competencies include empathy, kindness, and gratitude; Insight competencies include self-knowledge and self-inquiry, a curiosity-driven

investigation of self-related beliefs and processes; and Purpose competencies include knowing what brings meaning, purpose, and fulfillment in one's life.

The STH draws from gold-standard, evidence-based mental health and stress coping interventions, such as Mindfulness-based Stress Reduction (MBSR; Kabat-Zinn, 1983), character interventions (Niemic, 2017), cognitive-behavior therapy (Beck, 2011), rational emotive behavior therapy (Ellis & MacLaren, 1998), and acceptance and commitment therapy (Bond, Hayes, Lillis, Luoma, & Masuda, 2006). For example, the STH includes mindfulness of breathing and body scan from MBSR; identification and questioning of cognitive distortions, and positive reappraisal from CBT and REBT; values clarification and committed action from ACT; and gratitude and mindful listening and speaking from CI. Developed by native Spanish speakers in Spanish for a Latin American audience, the STH has been culturally adapted for its intended audience (Benish, Quintana, & Wampold, 2011). Cultural adaptation of behavioral interventions has been shown to improve efficacy (Benish et al., 2011). The result is a training that is culturally relevant, comprehensive, simple, and easy to learn and apply.

To date, the STH has been implemented with over 3200 Mexican HCPs (i.e., physicians, nurses, residents, social workers, psychologists, lab technician, technicians, and administrative staff). In a pilot study with 502 HCPs conducted between October and December 2020, feasibility and acceptability were evidenced by the 81% of participants who completed at least 6 of 8 sessions, and the high ratings of program content, instruction, and perceived benefits (9.8/10). Preliminary data on program efficacy collected from 258 participants who volunteered to provide pre- and post-program data are encouraging. Although effects sizes are likely inflated through selection bias, participants reported significant pre- to post-test reductions in depression ( $d=0.81$ ), anxiety ( $d=0.58$ ), stress ( $d=0.65$ ), and occupational burnout (emotional exhaustion  $d=1.20$ ; personal accomplishment  $d=0.98$ ; Supplementary Materials).

### **Healthy Minds Program**

The Center for Healthy Minds (CHM) at the University of Wisconsin-Madison has recently developed a character-based mHealth meditation intervention called the Healthy Minds Program (HMP, Figure 2), organized around the ACIP model of well-being (Dahl et al., 2020). The HMP app is freely available throughout the world. A unique feature of the HMP is that it has been designed to be used amidst the business of daily life. Short, podcast style lessons on the science of well-being from world-renowned scientists are paired with instruction in meditation practices that are highly flexible. Guided practice can be done as a sitting meditation or active practice, with the latter designed to be carried out during simple daily activities, such as eating or going for a walk. Individuals can also choose between different guides and different lengths, ranging from 5 to 30 minutes, allowing maximum individualization.

Two randomized controlled trials (RCTs) of the HMP have demonstrated that even at very low dosages (on average <5 min/day for one month), the program results in a range of positive outcomes related to mental health, human flourishing, and character strengths. Goldberg and colleagues (Goldberg et al., 2020) examined an 8-week iteration of the HMP in the general population ( $N=343$ ) and reported significant HMP effects on psychological distress and loneliness. Hirshberg et al. (M. J. et al. Hirshberg, 2021) conducted a fully remote RCT with public school educators ( $N=662$ ) during the COVID-19 pandemic. Using a 4-week version of the HMP, they reported significant HMP effects on the primary outcome of psychological distress and on all secondary ACIP character outcomes (e.g., mindfulness, self-compassion, cognitive distancing). All intervention effects persisted at the three-month follow-up compared to the wait list control group. Also important, no evidence for adverse effects were found, and the benefits

of the app were at least as large in the subsample of participants reporting elevated anxiety and depression at baseline (>50% of the sample).

### Integrating the STH and the HMP.

The Center for Healthy Minds (CHM) and AtentaMente will integrate the STH with the HMP. The resulting ISTH program will be a 12-week intervention that consists of an initial eight-week synchronous and app-supported training, followed by an additional four-weeks of app-only training. Employing the best practices both CHM and AtentaMente have honed over past projects, the synchronous components will be delivered through Zoom and recorded, to allow for asynchronous participant engagement if required, and app implementation will be carried out in accordance with the strategies Hirshberg et al. (2021) used successfully (most important is immediate contact with non-adhering participants). The ISTH has the potential to represent a significant step toward fulfilling the urgent need to support HCP well-being in Mexico and longer-term, Latin America.

The STH and the HMP are well-suited to integration. They are constructed around the same theory of change (Figure 1) and model of well-being (i.e., ACIP model), make use of declarative and procedural learning strategies, and provide instruction in many of the same foundational meditation practices. For example, both interventions employ short lessons that teach the key principles underlying a character strength leading to declarative learning about this strength, and follow declarative learning with guided meditations and exercises tailored to daily life experiences where the strength is practiced and applied (procedural learning). The major work of this integration is synchronizing the scope and sequence of the two programs so that users receive a seamless, uniform program, and constructing a modest amount of new content (4 new “learn” podcasts, eight new guided practices) for the four-week fully remote component of the training.

**Figure 1. Theory of Change**

[figure not shown]

## 4. STUDY DESIGN

A two-arm parallel RCT with a wait-list controlled design in which the control group may pursue professional development activities as usual and will receive access to the intervention following the final study assessment nine-months post-randomization. Assessors will be blind to group assignment. Target sample sizes were determined based on power analyses. The unit of randomization is the individual participant. The co-primary outcomes are psychological distress and well-being. Participants will complete assessments at baseline, prior to random assignment, after weeks one, three, five, eight and twelve (i.e., post-intervention), and after weeks 24 and 36. A subset of 510 participants (255 from each condition) will be selected for a dried blood spot substudy in which dried blood samples will be collected at baseline, week 12 and week 24. A subset of 510 participants, ideally overlapping with the dried bloodspot substudy, will be selected for the patient satisfaction substudy in which enumerators assess participants' patients perspectives on their care.

#### **4.1 Number of subjects**

Data will be collected from an anticipated sample of up to 4,000 Mexican healthcare providers who work in a participating healthcare system within a participating Mexican State (Campeche, Coahuila, Guanajuato, Jalisco, Nuevo Leon, Oaxaca, Queretaro, or Sonora).

#### **4.2 Subject Selection and Withdrawal**

##### **4.2.1.1 Inclusion and Exclusion Criteria**

Inclusion Criteria:

- $\geq 18$  years old
- Employee in a participating healthcare system in a participating Mexican State

Exclusion Criteria:

- $<18$  years old
- Not in a participant healthcare system in a participating state
- Does not work in a qualifying healthcare provider role
- Does not have regular access to reliable internet and/or a smartphone capable of downloading the Healthy Minds Program app

#### **4.3. Screening, Recruitment, and Enrollment**

##### **4.3.1 Screening**

Participants will enter into the study REDCap project and complete a preliminary eligibility screen. Those deemed eligible will be sent a follow-up invitation to provide additional information to determine final study eligibility and be provided a detailed summary of study activities and the study timeline.

##### **4.3.2 Recruitment and Enrollment**

Recruitment will occur through informational sessions at large regional healthcare facilities and internal communications from the Minister's of Health in each participating state. Participants will self-enroll via the REDCap study project as described in screening.

##### **4.3.4 Early Withdrawal**

Participants may withdraw at any time by requesting withdrawal from the study team.

## **5 STUDY INTERVENTION**

The Integrated Stress Toolbox for Healthcare providers (ISTH) is a 12-week meditation-based well-being training. In weeks 1-8, participants engage in weekly 2-hour class sessions that are recorded and posted on a private Youtube channel. There is a final two-hour session at week 12. In-class learning is augmented and extended through content in a special version of the Healthy

Minds Program smartphone app that participants are asked to use on a daily basis throughout the intervention.

## **6 OUTCOME MEASURES**

### **6.1 DEFINITION AND ASCERTAINMENT OF OUTCOMES**

Outcomes were selected to assess the general and occupational specific psychological factors theoretically and empirically associated with improved mental health, well-being and occupational outcomes.

#### **6.1.1 Primary Outcomes**

Study co-primary outcomes are distress, operationalized as the z-scored aggregate of Patient-Reported Outcomes Measurement Information System (PROMIS) Depression (8-items) and Anxiety (8-items) Scales, and the NIH Toolbox Perceived Stress v2.0 (10-items) and well-being, measured with the World Health Organization Five Well-Being Index (WHO-5). The WHP-5 is a short self-reported measure of current mental well-being (time frame the previous two weeks). Higher distress scores indicate greater symptoms of psychological distress and higher well-being scores (range 0 lowest possible well-being to 25 highest possible well-being) indicate greater well-being.

#### **6.1.2 Secondary Outcomes**

Secondary Outcomes consist of: the Healthy Minds Index (17-items), a measure of four components of well-being – awareness, connection insight and purpose; Gratitude Questionnaire 6 (6-items); and the Maslach Burnout Inventory Emotional Exhaustion and Personal Accomplishment subscales (15-items).

Administrative records. We will receive prior, current and next year employment records on participants, including, number and reasons for absences and type of employment. Biomarkers - Dried blood spot substudy: CRP, IL-6, IL-10, TNFalpha.

#### **6.1.3 Tertiary (Mechanistic) Outcomes**

Five Facet Mindfulness Questionnaire Act with Awareness and Nonreact to inner experience subscales (FFMQ; Baseline, after weeks 3, 8, and 12); Interpersonal Reactivity Index Empathic Concern subscale (IRI-Empathic Concern; baseline, after weeks 5, 8 and 12); Cognitive Emotion Regulation Questionnaire reappraisal subscale (CERQ- Emotion regulation; baseline, after weeks 3, 5, 8, and 12); Meaning in Life Questionnaire Presence subscale (ML- Presence; baseline, after weeks 1, 8 and 12); MAIA self-regulation subscale (baseline, after weeks 1, 3, 8, 12); Compassionate Engagement and Action Scale Compassion for others subscale (CEAS; baseline, after weeks 8 and 12); Global Assessments of Character Strengths 24 (GACS; baseline, after weeks 12 and 36).

## **7 STUDY PROCEDURES AND VISITS**

### **7.1 Randomization**

Using stratified random permuted blocks of 4, with Mexican State and the tier of healthcare facility as the strata, participants will be randomly assigned 1:1 to either the ISTH or wait-list control. The randomization list will be entered into REDCap and participants will be auto-assigned based on strata via REDCap's assignment features (i.e., no experimenter involvement).

### **7.2 Schedule of Events**

| Event                                         | Prescreen | Baseline | Wk 1 | Wk 3 | Wk 5 | Wk 8 | Wk 12 | Wk 24 | Wk 36 |
|-----------------------------------------------|-----------|----------|------|------|------|------|-------|-------|-------|
| Screening and Stratification Measures  |           |          |      |      |      |      |       |       |       |
| Informed Consent                              |           | X        |      |      |      |      |       |       |       |
| Demographics                                  | X         | X        |      |      |      |      |       |       |       |
| Primary and Secondary Outcomes         |           |          |      |      |      |      |       |       |       |
| PROMIS Anxiety, Depression & Perceived Stress |           | X        | X    | X    | X    | X    | X     | X     | X     |
| WHO-5                                         |           | X        | X    | X    | X    | X    | X     | X     | X     |
| Healthy Minds Index                           |           | X        | X    |      | X    | X    | X     |       |       |
| GQ-6                                          |           | X        |      |      | X    | X    | X     |       |       |
| Maslach Burnout Inventory                     |           | X        |      |      |      | X    | X     | X     | X     |
| Dried blood spots                             |           | X        |      |      |      |      | X     | X     |       |
| Tertiary Outcomes (Mechanisms)         |           |          |      |      |      |      |       |       |       |
| FFMQ                                          |           | X        |      | X    |      | X    | X     |       |       |
| IRI- Empathic Concern                         |           | X        |      |      | X    | X    | X     |       |       |
| CERQ - Reappraisal                            |           | X        |      | X    | X    | X    | X     |       |       |
| ML- Presence                                  |           | X        | X    |      |      | X    | X     |       |       |
| MAIA Self-regulation                          |           | X        | X    | X    |      | X    | X     |       |       |
| CEAS                                          |           | X        |      |      |      | X    | X     |       |       |
| GACS                                          |           | X        |      |      |      |      | X     |       | X     |

## 8 STATISTICAL ANALYSIS, SAMPLE SIZE AND POWER CALCULATIONS

### 8.1 DESIGN OVERVIEW

This is a two-arm parallel RCT with a wait-list controlled design in which the control group may pursue professional development activities as usual and will receive access to the intervention following the final study assessment nine-months post-randomization. We will enroll up to 4,000 participants within the recruitment window, which closes on May 21, 2023.

### 8.2 SAMPLE SIZE AND POWER ANALYSES

Our target sample size was informed in part by our agreements with State Ministers of Health, which requested a minimum number of participants from each participating state. Because of the large, planned sample size (up to 4,000), we conducted two power analyses. First, we conducted a sensitivity power analysis to determine the smallest detectable effect based on the lower bound of the expected intention-to-treat sample of 4,000. To ensure our power estimates were conservative, we based power calculations off of the Bonferroni corrected two-tailed p-value assuming that all primary and secondary outcomes in the parent trial share the same family-wise error 0.05 error rate. We plan to test a total of 9 primary and secondary outcomes for a Bonferroni corrected error rate of 0.006. For measures collected at all 10 assessments points, we assume:

- 0.80 power
- A correlation of  $r = .50$  between the same measure at different assessments
- Error rate of 0.006

Under the above conditions, we will be able to detect a significant group by time interaction effect of Cohen's  $d \geq 0.04$ . For measures assessed at five of the timepoints, assuming the same conditions listed above, we will be able to detect between group effects of Cohen's  $d \geq 0.05$ .

We conducted a second power analysis to determine the size of the randomly selected biomarker and patient satisfaction report subsample required to detect a pre- to post-test change of  $d \geq 0.15$ . We selected  $d \geq 0.15$  as our expected effect size because, in two meta-analyses on the topic of mindfulness-based interventions effects on inflammation,  $d \geq 0.15$  was the smallest observed average effect size on the cytokines we will assay. We assume:

- 0.90 power
- A correlation of  $r = .60$  between the same measure at different assessments
- Error rate of 0.005

In order to detect a statistically significant group by time interaction effect of Cohen's  $d \geq 0.15$  on our measures of peripheral inflammation, we will require a subsample of 468 participants. Assuming 10% of selected participants do not provide a pre-test sample, we plan to randomly select 255 participants from each group (510 total) to participate in biomarker data collection.

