### 8.4 STATISTICAL ANALYSIS PLAN

See <https://osf.io/9g58j> for preregistration of statistical plan, hypotheses and outcomes.

Primary and secondary outcomes will be analyzed using linear mixed effects models with time nested within participant. All randomized participants will be included (i.e., intention-to-treat analyses). Maximum likelihood estimation will be used for missing data. To help determine the best fit for modeling change over time, we will plot outcomes over time by group using loess regression. We will then quantitatively compare the Akaike Information Criterion (AIC) and Bayesian Information Criterion (BIC) of candidate models of linear change, loglinear change, polynomial change, and piecewise linear change in which change over the intervention period is modeled separately from change over follow-up. Primary effects of interest are groupXtime interactions from pre- to post, pre- to 3-month follow-up, and pre- to six month follow-up. We will control for gender and age. Models with and without social desirable responding will be compared and the best fitting model will be used.

Covariates may be centered to aid in model interpretation. Statistical significance will be set at a two-tailed alpha of  $p < 0.05$ , false discovery rate corrected for the 9 inferential tests at post-test (2 primary, 7 secondary outcomes) and the three inferential tests at 6-month follow-up. In addition to statistical significance, magnitude of differences will be estimated using standardized mean differences on continuous outcomes and Odds Ratios on binary outcomes.

Before hypothesis testing, we will use the "careless" package in R to check for patterns of aberrant responding on the survey items. Should evidence for inattentive responding be observed, we will report results with and without affected data removed. Given the expected sample size, we do not expect outliers or high leverage points to be observed but we will use simulation methods to check models for these points. Should high influence points be observed, we will report models with and without them.

Should evidence for data not missing at random be observed (e.g., differential attrition between groups, inability to predict missingness based on observed variables) we will conduct pattern-mixture modeling.

We will examine moderation of intervention effects on primary and secondary outcomes by participants gender, age, employment type and location.

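### The parent trial's stated detectable effects (d of 0.04 and 0.05) are not differences in change for the planned contrasts; the simple pre-to-post contrast detects about 0.11 SD at N = 4,000, and the number of visits and the N used need reconciling.

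*Protocol*

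**What the plan says.** Protocol section 8.2 gives a sensitivity calculation for the parent trial.

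- **Sample size:** "based on the lower bound of the expected intention-to-treat sample of 4,000".
- **Error rate:** "We plan to test a total of 9 primary and secondary outcomes for a Bonferroni corrected error rate of 0.006", two-tailed.
- **Visits:** "For measures collected at all 10 assessments points, we assume" 0.80 power and a correlation of .50 between assessments.
- **Result:** "we will be able to detect a significant group by time interaction effect of" d ≥ 0.04, and d ≥ 0.05 for measures taken at five timepoints.

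The section names no formula or test.

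Other sections bear on this:

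- Section 8.1: "We will enroll up to 4,000 participants within the recruitment window". Sections 4.1 and 8.2 also give 4,000 as an upper limit.
- Section 4: assessments at baseline and "after weeks one, three, five, eight and twelve (i.e., post-intervention), and after weeks 24 and 36", which is eight. The table in section 7.2 agrees.
- Section 8.4: "Primary effects of interest are groupXtime interactions from pre- to post, pre- to 3-month follow-up, and pre- to six month follow-up", from linear mixed models whose time form (linear, loglinear, polynomial or piecewise) is chosen by AIC and BIC. Effect size is to be reported as a standardized mean difference.

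**The concern.** A reader will take d in section 8.2 to be on the scale that section 8.4 reports: the between-arm difference in change, in SD units. For a two-arm trial of 4,000, a detectable difference of 0.04 SD looks far too small. Section 8.2 presents its calculation as conservative, so the figure invites trust.

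What is at stake is the reading of the results. If 0.04 were right, a null result on distress or WHO-5 would argue against any effect above 0.04 SD. If the detectable difference is two to three times larger, it would not. The calculation also rests on a number of visits that the trial does not have, and on an N that the text describes in two incompatible ways.

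**Working it through.** **Inputs.** N = 4,000, two-sided alpha 0.006, power 0.80 and r = .50 (section 8.2); 1:1 allocation, so n = 2,000 per arm (section 7.1); eight visits at weeks 0, 1, 3, 5, 8, 12, 24 and 36 (sections 4 and 7.2). The outcome SD is set to 1. z(0.997) + z(0.80) = 2.748 + 0.842 = 3.589.

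**1. Reproducing the plan's figures.** No two-visit formula gives 0.04 or 0.05. The nearest source is the omnibus group-by-time F test of repeated-measures ANOVA, with noncentrality λ = f²·N·m/(1 − r), degrees of freedom m − 1 and (N − 2)(m − 1), reported as d = 2f:

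| N | m = 10 | m = 8 | m = 5 |
|---|---|---|---|
| 4,000 | 0.034 | 0.037 | 0.043 |
| 2,900 | 0.040 | 0.043 | 0.050 |

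At N = 4,000 the stated values appear only if rounded up; power at 0.04 (m = 10) and 0.05 (m = 5) would be 0.95 and 0.94. At about 2,900 both match. The same method with three assessments, r = .60, alpha 0.005 and 90% power gives 464 for the biomarker substudy, against the stated 468. That supports this origin, but it remains an inference.

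**2. What 2f measures.** Here 2f is the SD, over visits, of the between-arm difference. It is not a difference in change. If the arms are equal at baseline and differ by a constant D afterwards, that SD is D·√[(1/m)(1 − 1/m)]:

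- m = 10: 0.3·D, so 2f = 0.034 means D = 0.034/0.3 = 0.113.
- m = 5: 0.4·D, so 2f = 0.0427 means D = 0.0427/0.4 = 0.107.

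So, under this pattern, the omnibus calculation itself points to about 0.11 SD on the scale of section 8.4.

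**3. Simple pre-to-post contrast.** The variance of a change score is 2(1 − r) = 1.0. The standard error of the difference is √(2 × 1.0/2,000) = 0.0316.

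- Detectable difference: 3.589 × 0.0316 = **0.1135**.
- Power at 0.04: 0.04/0.0316 = 1.265, which gives **7%**. At 0.05 it is 12%.
- Needed per arm to detect 0.04: 2 × 3.589²/0.04² ≈ 16,105.
- At an uncorrected alpha of .05: 0.089, with 24% power at 0.04.
- If 3,000 are analysed (assumption): 0.131. If 2,000 (assumption): 0.161.

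**4. Mixed models over all eight visits.** These use generalized least squares with correlation .50 between all visits, no random slopes, no missing data and log(week + 1) for the loglinear form. Those are assumptions. The value is 3.589 times the standard error of the modelled difference in change at week 12, N = 4,000:

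| Time form | Week 12 |
|---|---|
| Piecewise (knot at week 12) | 0.091 |
| Quadratic | 0.075 |
| Loglinear | 0.063 |
| Linear to week 36 | 0.029 |

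In the linear case the weeks' sum of squares is 2,115 − 89²/8 = 1,124.9. The slope's standard error is √(2 × 0.5/(2,000 × 1,124.9)) = 0.000667, and 3.589 × 12 × 0.000667 = 0.029. The same slope is three times that at week 36: 0.086.

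**5. Visits and N.** Section 8.2 has 10 assessments; sections 4 and 7.2 have 8. Section 8.2 calls 4,000 a lower bound; sections 4.1, 8.1 and 8.2 itself make it an upper limit. No smaller N is printed.

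**The case against.** **The planned analysis is not a two-visit contrast.** This stands. A reader might infer that one true figure, about 0.10 to 0.11, should replace 0.04. The protocol does not support that: section 8.4 leaves the time form open, and the eight-visit models give 0.06 to 0.09 at week 12. One listed candidate, linear change to week 36, does go below 0.04. It does so only by assuming that benefit keeps growing at the same rate for 24 weeks after training ends.

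**A baseline-adjusted analysis would do better.** It would detect 0.098. But section 8.4 lists gender and age as covariates and treats baseline as a time point, so this is not a stated analysis and should not set the replacement figure.

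**The N may already be conservative.** A reader might infer that section 8.2 used the maximum and allowed no loss. That is not shown. The phrase can be read as a lower bound on an expected 4,000, and the inferred method matches both stated values at about 2,900. What stands is that the text does not say which N was used.

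**Alpha.** Section 8.4 uses false discovery rate control, which can be more lenient than Bonferroni. Even at .05 the simple contrast detects 0.089, about twice the stated value.

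**Practical weight.** The N was partly set by agreements with state ministries, and section 8.1 has recruitment closing in May 2023. No design choice is shown to rest on these sentences.

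**Conclusion.** The point holds and should be fixed, but it does not undermine the design. The stated 0.04 and 0.05 are not standardized between-arm differences in change for the contrasts in section 8.4.

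For the simple pre-to-post contrast at N = 4,000, sensitivity is overstated by 0.1135/0.04 = 2.8 for measures at every visit and 0.1135/0.05 = 2.3 for those at five. For the co-primary outcomes, modelling all eight visits narrows the gap to between 0.063/0.04 = 1.6 and 0.091/0.04 = 2.3 at week 12, unless the trend is strictly linear to week 36. These sizes rest on r = .50 between all visits, no random slopes and complete data; loss would raise them. The 2f origin is inferred, and the conclusion does not depend on it.

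Two contradictions stand regardless: 10 assessments against 8, and a lower bound against an upper limit. Correcting only the visit count moves the inferred 2f from 0.034 to 0.037, so that alone is minor.

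A reader might infer that the trial is too small. It is not shown to be: 0.11 SD is still a small effect.

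**What to change.** In section 8.2, replace both detectable-effect sentences with the detectable standardized difference for the planned week-12 contrast, naming the test, the effect-size scale and the N used. For example:

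*At the maximum N of 4,000 (two-sided alpha .006, 80% power, r = .50), the detectable between-arm difference in pre-to-post change is about 0.11 SD for the unadjusted two-visit contrast, and about 0.06 to 0.09 SD at week 12 if a loglinear, quadratic or piecewise model over all eight visits holds. If 3,000 are analysed (an assumption), the two-visit figure is about 0.13 SD.*

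The 0.06 to 0.09 range applies to measures taken at all eight visits; measures taken at five need their own model-based figure.

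Change 10 assessments to 8. Reconcile the lower-bound phrase with the upper limit of 4,000 by stating the N that was actually used. If the original figures are kept for the record, label them as 2f from an omnibus interaction test, once the authors confirm that this is what they are.

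The cost is wording only. The stated sensitivity becomes less favourable.
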